## Method

### Design

This study will use a parallel two-arm cluster randomised control trial (cRCT) with equal allocation of schools to intervention or waitlist control conditions (see Fig. 1). Teachers in schools assigned to the intervention condition will receive training and will deliver the BodyKind programme to students, while the waitlist control will receive classes as usual. This will be a pragmatic trial, conducted under ‘real world’ conditions i.e., in a school setting, with teacher-led delivery during class time over a four-week period (1 lesson each week). Outcomes will be measured at three time points (pre-, post- and two-month follow up). As per [54], a two-month follow up was selected to fit within the academic school year. Waitlist control schools will complete teacher training and the BodyKind programme after the completion of measures. This study received ethics approval from University College Dublin University (HS-22-71) and was retrospectively registered on 10/10/2023 on ClinicalTrials.gov, NCT06076993.

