### Participants

We aim to recruit a total of 600 students aged 15-17 years in Senior Cycle: Transition Year (a non-academically structured year in Irish secondary schools designed to facilitate the pursuit of alternative interests and self-discovery). An RMASS power analysis [55] based on parameters; small Cohen’s d effect size of .2, power .80, alpha .05, indicates that 504 students are required. A small effect size was selected in line with a meta-analysis of schools-based interventions for body image outcomes [14] which observed small effect sizes (d=.22 - .48) which despite being described as ‘small’ can have important real-world impact, particularly when scaled up across a whole school population [56]. To account for natural attrition and unanticipated events that reduce participant numbers (e.g., student absence due to illness) in cRCTs, we will recruit approximately 20% (*n=*100) more participants giving a total *N=*600. Given the variability in class size in Transition Year range in consent rates for active parental consent [57], and to guard against drop out at a cluster level we will recruit a minimum of 12 schools and a maximum of 26 schools with 1-2 fully qualified second-level teachers per school (range 12-52 teachers). Schools will be eligible if they are a second-level school in the Republic of Ireland that offers the Transition (TY) programme to students. Only data from full-time TY students aged 15-17 years (i.e., not exchange or short-term visiting students) will be included in analyses.

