#### Data analyses

Generalised linear mixed effects models (GLMM) will be used to determine change on outcome measures. Primary analysis will compare measures at time one (baseline) and two (post-intervention), to identify fixed effects of the intervention. Potential clustering effects will be examined and accounted for at the school level. The model will include 2 main effects (Repeated measures effect of Time and Between subjects’ effect of Condition) and one two-way interaction Time*Condition). Gender effects will also be considered. With gender in the analyses, the model will have three main effects and corresponding two-way and three-way interactions. Secondary analyses will examine data from time 3 (follow-up) to see if the intervention condition has maintained hypothesised changes in dependent variables. We will also assess the proportion of within-group and between-group variance by calculating the Intra Class Correlation (ICC). As complex models can fail to converge, if we encounter convergence issues in our models, we may consider dropping the random effect accounting for the smallest proportion of between-group variance.

Mediation analyses will investigate whether body ideal internalisation, self-compassion and compassion for others mediate change in outcomes of body dissatisfaction and positive body image from T1 to T2 in the intervention condition. Moderation analyses will investigate whether appearance-related social media use, appearance teasing, gender, school type, baseline body appreciation, body dissatisfaction, psychological wellbeing and implementation quality moderate changes from T1 to T2.

Exploratory analyses will investigate the extent to which results are sensitive to floor effects which are common in universal body image interventions. We will conduct a mixed-effects regression model that includes participants who report moderate levels of body dissatisfaction (i.e., boys and girls who score 1.5 standard deviations below mean for body dissatisfaction of their respective genders).

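### The convergence fallback does not exempt the school-level random effect, so a school-randomised trial could lose the term that protects its primary test

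*Protocol article*

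**What the plan says.** The Design section describes "equal allocation of schools to intervention or waitlist control conditions", so the school is the unit of randomisation. The Data analyses section specifies mixed models with Time, Condition and their interaction, with baseline against post-intervention as the primary comparison. On clustering it says: "Potential clustering effects will be examined and accounted for at the school level". Later in the same paragraph comes the fallback: "if we encounter convergence issues in our models, we may consider dropping the random effect accounting for the smallest proportion of between-group variance".

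School is the only clustering level named. The article does not list the random effects, gives no ICC (it will be estimated from the data), and names no alternative analysis for use when a model fails to converge. The Participants section plans for 12 to 26 schools and 600 students.

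**The concern.** The fallback chooses what to remove by the size of a variance, not by the term's role in the design. In a cluster trial the school-level term on the tested contrast has to stay however small its estimate, because without it students are treated as if each had been randomised separately.

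The rule can point at school on either reading of its wording. If it ranks all random effects, school variance is likely to be small beside student variance in repeated self-report data (a judgement, as the article gives no figure). If between-group means between schools, only school-level terms are in the ranking.

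Between-school variation in change is not remote here. One or two teachers per school deliver the lessons. Hypothesis 7 in the Background expects implementation to differ between schools, with possible consequences for effectiveness. If that variation exists and its term is removed, standard errors are too small and an ineffective programme is declared effective too often.

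**Working it through.** **Plan's own figure.** The article states no error rate for the fallback. The only benchmark is the nominal level in "power .80, alpha .05" (Participants), taken here as two-sided because sidedness is not stated.

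**Inputs.** From the article: 600 students ("We aim to recruit a total of 600 students aged 15-17 years") and 26 or 12 schools, so m = 600/26 = 23.1 or 600/12 = 50 per school. Assumed: an ICC of the tested contrast (the pre-post change) of 0, .01, .02 or .05.

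**Formula.** With the school-level term omitted:
- design effect: DEFF = 1 + (m − 1) × ICC
- true type I error = 2 × [1 − Φ(1.96/√DEFF)]

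At ICC = 0, DEFF = 1 and the formula returns the nominal .05. For example, at m = 50 and ICC = .02, DEFF = 1 + 49 × .02 = 1.98, 1.96/√1.98 = 1.39, and the error is .164.

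| Schools × students | ICC of change | DEFF | Type I error | Simulated, school omitted |
|---|---|---|---|---|
| 26 × 23 | .01 | 1.22 | .076 | .077 |
| 26 × 23 | .02 | 1.44 | .103 | .103 |
| 26 × 23 | .05 | 2.10 | .177 | .179 |
| 12 × 50 | .01 | 1.49 | .108 | .110 |
| 12 × 50 | .02 | 1.98 | .164 | .164 |
| 12 × 50 | .05 | 3.45 | .291 | .299 |

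With the 504 students required before the attrition allowance (504/26 = 19.4 and 504/12 = 42 per school), the formula gives .072/.094/.157 and .099/.146/.262 at the same ICCs.

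**Keeping school.** A school-level test of change held the simulated error at .046 to .053 in every scenario.

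**Which school term matters.** A school intercept that is constant over time cancels from the pre-post difference. With an intercept ICC of .02 or .05, no school-by-time variance and an assumed T1-T2 correlation of .7, omitting school left the simulated Time × Condition error at .048 to .051. In a baseline-adjusted T2 model the intercept does not cancel fully. Under the same conditions, omitting it gave .061 to .071 (26 schools) and .067 to .103 (12 schools). The term to protect is therefore school-by-time in the first model and the school intercept in the second.

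**Dropping only at a zero estimate.** If school were removed only when its variance was estimated as zero, the overall error stayed at .033 to .053. Within the runs where it was removed, the error was about .08 to .16 (26 × 23) or .11 to .30 (12 × 50) for a change ICC of .01 to .05.

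**The case against.** The strongest reply is that the fallback is optional and conditional. It needs non-convergence and then a decision to drop, and the paragraph containing it also commits to school-level clustering. The random effects are not listed, so the smallest might not be a school term. If both a school intercept and a school-by-time term are fitted, losing the intercept does the stated test no harm. These points stand, and they limit the claim to what the rule permits.

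They do not remove it. The rule has no exemption for school and no condition that the variance be estimated as zero. Discretion is itself a weakness: the limitations section says researchers cannot be blinded, and three primary outcomes could end up with different error structures.

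Three stronger readings are tempting but unsupported:
- A reader might infer that the school term will be dropped and every primary outcome affected. The article does not show which term is smallest or that any model will fail.
- A reader might infer an error of 2 to 6 times nominal. That needs the drop to occur and a change ICC of about .02 to .05. At .01 with 26 schools the ratio is .076/.05 = 1.5, and at 0 it is 1. The top value also needs the minimum of 12 schools.
- A reader might take "indicates that 504 students are required" as evidence of a high pre-post correlation, and so of a dominant student variance. The correlation input is not given. A total near 504 arises with r of about .45, .60 or .68, depending on the repeated-measures design assumed.

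Whether a school-by-time term is fitted at all is detail that an article can leave to the full plan, and it is not counted here.

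**Conclusion.** The point holds in conditional form. The fallback permits removal of a school-level random effect in a school-randomised trial, in conflict with the commitment earlier in the same paragraph. This is a rule fixed badly, not a missing detail.

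If the term carrying between-school variation in change is the one removed, the type I error runs from nominal (ICC 0) to about 18% with 26 schools or 29% with 12, at an assumed change ICC of .05. If only a time-constant school intercept is removed, the Time × Condition test is essentially unaffected. The sizes rest on the assumed ICCs, equal school sizes and the drop taking place. The article fixes none of these, and it does not say how likely the drop is.

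**What to change.** Replace the fallback with wording such as:

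*The school-level random effect on the tested contrast (school-by-time in the Time × Condition model, or the school intercept in a baseline-adjusted T2 model) is exempt from removal. If a model does not converge, we will first change the optimiser or simplify other terms; if that fails, we will compare school-level baseline-adjusted means between arms with a t-test on (number of schools − 2) degrees of freedom.*

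That is 24 degrees of freedom with 26 schools and 10 with 12. A small-sample degrees-of-freedom method for the mixed model, such as Kenward-Roger or Satterthwaite, is optional.

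The cost is two sentences, with no change to data collection or recruitment. Intervals will be wider than those from a model without school, by about √DEFF. At ICCs of .01/.02/.05 that is 1.10/1.20/1.45 times with 26 schools and 1.22/1.41/1.86 times with 12. This extra width reflects real uncertainty that a model without school would hide.

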### Implementation quality evaluation

Implementation dimensions of: (i) dosage, (ii) adherence, (iii) quality of delivery, and (iv) responsiveness will be averaged to provide a total implementation quality score. Correlations will be used to explore relationships among the dimensions. Implementation quality will be explored as a moderator of intervention effectiveness.

As per [52], Total Implementation Quality = (Total Dosage + Total Adherence + Total Quality of Delivery + Total Participant Responsiveness) / 4.

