### Procedure

Informed active consent will be sought from school principals (during recruitment) and we will also seek informed consent from teachers (before teacher training), parents (before baseline assessment) and assent from students (at baseline assessments). On receiving principal consent to participate, the researcher will liaise with a nominated staff member to coordinate involvement. Optional virtual ‘zoom check in’ meetings with the primary researcher will be offered to parents and students prior to participation in addition to teachers throughout the trial to address queries/issues about the programme/research. Students without consent to participate will be given the option to attend supervised study period or another school-based activity during time allotted to the intervention. Participants can withdraw from participation at any point without explanation.

Data will be collected via participant self-report to standardized questionnaires delivered in an online format using an online platform (e.g., SurveyMonkey) or in pen and paper format (as per the preferences of the school). Questionnaires will be administered to students by a member of the research team under exam-like conditions. In the post-intervention questionnaire, students in the experimental group will be asked additional questions about their perceptions of the programme. Teachers in the experimental group will also complete fidelity checklists after each lesson and a short questionnaire on completion about perceptions of the programme. On study completion, participants will receive a full debrief and contact details for relevant support services. Schools will receive a €200 financial honorarium for participating.

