### Implementation quality evaluation

Four dimensions of implementation quality will be assessed; 1. dosage (number of sessions delivered/attended), 2. fidelity (extent to which programme is delivered as intended), 3., quality (how well the programme is delivered by the facilitator), and 4., responsiveness (how well participants engage with the programme). As per Dowling & Barry [52], dimension scores will be combined to yield a total implementation quality index score which indicated schools as either high- or low- implementors. Dimensions will not be weighted as each dimension is considered equally important in this implementation quality index. Qualitative data will be used to expand on potential factors influencing programme implementation.

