#### Dosage

Will be assessed via two indicators. 1.) Teachers will indicate if they delivered the lesson (Yes=1, No=0) and this will be summed across all four lessons, 2.) Students will indicate on the Student Feedback Questionnaire (Yes=1, No=0) if they remembered attending each of the four lessons, this will be summed across all lessons and student scores will be averaged for each school.

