#### Fidelity

Although observational methods (i.e., audio recordings) are considered gold standard for assessing fidelity, they are time and resource intensive and may change behaviours of those being observed. Self-report checklists are widely used as practical and acceptable measures to assess fidelity [73, 74].

Fidelity, will be measured via two indicators. 1.) Teachers will indicate (1=yes, 0=no) whether they covered the key items/concepts on fidelity checklists for each lesson. There are 7 items on the checklist for each lesson, which will be summed across all lessons. 2.) In post-intervention questionnaires, teachers will be asked to indicate the degree to which they implemented the programme as instructed in the teacher training manual using visual analogue scales ranging from (0=Not at all, 100 = Very Much So).

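### The implementation index adds dimensions on unlike scales despite declaring them equally important, and an index measured only in intervention schools is described as moderating the intervention effect

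*Protocol article*

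**What the plan says.** Under Data analysis, Implementation quality evaluation, the protocol article fixes the index: "Total Implementation Quality = (Total Dosage + Total Adherence + Total Quality of Delivery + Total Participant Responsiveness) / 4". The section of the same name under Method states the intent: "Dimensions will not be weighted as each dimension is considered equally important in this implementation quality index". That section also uses the total to class schools as high or low implementers.

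The scoring sections then define the components:

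- **Dosage:** "Teachers will indicate if they delivered the lesson (Yes=1, No=0) and this will be summed across all four lessons". For the students' recall of attending each lesson, "this will be summed across all lessons and student scores will be averaged for each school".
- **Fidelity** (called adherence in the formula): "There are 7 items on the checklist for each lesson, which will be summed across all lessons", plus a 0-100 teacher VAS.
- **Quality of delivery:** one student VAS and one teacher VAS, each 0-100.
- **Responsiveness:** 0-100 VAS scores from students and teachers, plus one student overall rating from 0 to 10.

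On use, Data analysis states: "Implementation quality will be explored as a moderator of intervention effectiveness". The Discussion lists implementation quality among potential moderators of intervention effects. On the source of the data, Procedure states: "Teachers in the experimental group will also complete fidelity checklists after each lesson". The sections on the student feedback questionnaire and the teacher questionnaire likewise collect these ratings only from those who received or delivered the programme.

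**The concern.** An unweighted sum of scores with unequal ranges is weighted by range. The stated formula therefore works against the stated principle of equal importance. The most concrete evidence of implementation, namely lessons delivered and checklist content covered, would have little say in which schools are classed as high or low implementers.

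The second part concerns interpretation. A moderator of a randomised effect must have a value in both arms. This index has none in control schools, which have classes as usual until measurement ends. Hypothesis 7, that implementation quality varies across schools and may affect effectiveness, would rest on a mis-scaled score. Under the present wording, a reader could also take an observational association for a randomised one.

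**Working it through.** The plan gives no figure for each dimension's share, so there is none to reproduce. The inputs are the indicator maxima in the sections Dosage, Fidelity, Quality of delivery and Responsiveness. Every indicator has a minimum of 0, so its maximum equals its range. The fourth responsiveness indicator (recommend, implement again, satisfaction) is taken as one 0-100 score.

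| Dimension | Indicator maxima | Averaged | Summed |
|---|---|---|---|
| Dosage | 4, 4 | 4 | 8 |
| Fidelity | 7 x 4 = 28, 100 | 64 | 128 |
| Quality of delivery | 100, 100 | 100 | 200 |
| Responsiveness | 100, 10, 100, 100 | 77.5 | 310 |
| Total | | 245.5 | 646 |

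**Share of attainable range = dimension maximum / total.** The division by 4 cancels.

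- Averaged: dosage 4/245.5 = 1.6%; fidelity 64/245.5 = 26.1%; quality 100/245.5 = 40.7%; responsiveness 77.5/245.5 = 31.6%.
- Summed: dosage 8/646 = 1.2%; fidelity 19.8%; quality 31.0%; responsiveness 48.0%.
- Equal importance would give 25% each.

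**Sensitivity to what is not stated.** Counting the fourth responsiveness indicator as two or three separate scores leaves dosage at 1.6% under averaging (4/250, 4/253). Under summing it falls to 1.1% (8/746) or 0.95% (8/846). If some dimensions are summed and others averaged, the extremes are:

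- Lowest: 4/(4 + 128 + 200 + 510) = 0.5%.
- Highest: 8/(8 + 64 + 100 + 77.5) = 3.2%.

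**Within dimensions, under averaging.** The 0-100 items contribute 50 (fidelity) + 100 (quality) + 75 (responsiveness) = 225, and 225/245.5 = 92%. The checklist contributes 14/245.5 = 6% and the 0-10 rating 2.5/245.5 = 1%.

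**In index points, under averaging.** Dosage falling from 4 to 2 lessons on both indicators lowers the index by 2/4 = 0.5. A 2-point drop on the 0-100 quality score does the same.

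**Moderator.** Participants gives 12 to 26 schools and Design gives equal allocation, so 6 to 13 schools have an index. If the index is set to any constant in controls, a school-level model with intercept, Condition, index and Condition x index has only three independent columns out of four. An interaction of the index with allocation therefore cannot be identified. What can be estimated is an association among intervention schools, or a non-randomised comparison of high implementers, low implementers and controls. Procedure places the students' programme ratings in the post-intervention questionnaire, so some index components share raters and occasion with the outcomes.

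**The case against.** The formula is attributed to a cited source that is not shown, and that source or a fuller plan may put indicators on a common scale. The article does not define a dimension total, and rescaling is the reading that best fits equal importance. This stands as a caveat: every percentage above assumes raw scores. It does not remove the conflict, because the article itself states the formula, the indicator ranges and the principle, and mentions no common scale.

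Share of attainable range is also not influence on ranking, which depends on how much schools differ. If nearly all schools deliver all four lessons, dosage will separate them little even after rescaling. That is correct. Rescaling removes an accidental weighting but does not guarantee equal influence. Nor do dimensions move in isolation: a school that skips lessons also loses checklist items.

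A reader might infer that schools would be ranked almost entirely on satisfaction ratings. The documents do not support this. Under averaging, fidelity and quality of delivery make up 26.1% + 40.7% = 66.8% of the range, and their items ask about adherence to the manual, teaching and teacher confidence. Responsiveness also covers understanding and attention.

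A reader might also infer that the plan specifies a Condition x index interaction that cannot be fitted. No section specifies one. Data analyses speaks of moderating change from baseline to post-intervention, which can be examined within the intervention arm. The difficulty lies in the wording of the Implementation quality evaluation section and the Discussion, which refer to intervention effectiveness and effects.

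**Conclusion.** The point holds on both parts, with limited reach. Followed as written, the formula contradicts the equal-importance statement. With raw scores, dosage carries about 1.2-1.6% of the attainable range when indicators are consistently summed or averaged, and 0.5-3.2% across mixed readings, against 25% intended. An unqualified claim that dosage counts for under 2% would go too far, because the within-dimension rule is not stated. Every reading is nevertheless far from 25%.

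The index is defined in one arm only and after randomisation, so it cannot support a statement about moderation of the randomised effect. A within-arm association in about 6-13 schools is legitimate if labelled as such. All of this concerns exploratory analyses. The primary Time by Condition comparison and the sample size do not depend on it.

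**What to change.** 1. Express each indicator as a percentage of its maximum: lessons/4, checklist/28, overall rating x 10, VAS scores as they are. Average indicators within each dimension, then average the four dimensions. Each dimension then has 25% of the attainable range. If the cited source already rescales, say so in one sentence.
2. State how indicators combine within a dimension, including whether the fourth responsiveness indicator is one score or several.
3. In the Data analysis section and the Discussion, replace the moderator wording for implementation quality with an exploratory, within-arm, school-level association. Label it non-randomised, and note that some components are rated by the students who report the outcomes.

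An instrumental-variable analysis with allocation as the instrument is not a way round this. It would need an index value in controls. It would also need allocation to act only through an index that includes teacher confidence and student enjoyment.

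The cost is scoring syntax and wording; no new data are needed.
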